#### *Time schedule for participants (see Table* 2*)*

**Table 2 Tab2:** **A schematic diagram of time schedule for enrolment, interventions, assessments, and visits for participants**

	Pre-randomization (day -7 to day 0): Check inclusion and exclusion criteria					
	Zelen's randomization					
	Parenteral nutrition group			Oral feeding group		
	Present "parenteral nutrition" info			Present "oral feeding" info		
	Day 1	Days 2-60*	Day 61-death**	Day 1	Days 2-60*	Day 61-death**
Obtain informed consent	X			X		
Record demographic data	X			X		
Take medical history	X			X		
*Treatment*						
Concomitant treatments	X	X		X	X	
Specific treatment (prior or ongoing)	X	X		X	X	
*Patient status*						
WHO Status	X	X	X	X	X	X
Karnofsky index	X	X		X	X	
Estimated life expectancy	X			X		
*Anthropometric data*						
Height	X			X		
Weight	X	X	X	X	X	X
*Biology*						
Lactic acid dehydrogenase	X			X		
C-reactive protein, albumin, prealbumin	X	X		X	X	
Blood count, electrolytes (including phosphorus, calcium, magnesium)	X	X				
Hepatic enzymes (AST, ALT, PAL, Gamma GT, Bilirubin)	X	X				
Triglycerides	X	X				
Ketonuria, glycosuria	X	X				
Quality of life questionnaires (QLQ-C15-PAL and QUAL-E***)	X	X	X	X	X	X
Socio-economic variables	X			X		
Dietetics consultation	X			X		
Ingesta questionnaire		X	X		X	X
Evaluation of metastatic disease		X			X	
Intervention supportive care		X			X	

*Follow-up consultation at least once per month **Evaluation once per month. ***Administer the QUAL-E if the patients consider themselves to be at the end of life (definition at the discretion of the physician and patient).

*Day -7 to day 0:* Patients who meet the inclusion criteria will be identified from medical files or from regular staff meetings or multidisciplinary case reviews, by the oncologist or the treating physician from palliative care. Once identified, eligible patients will be randomized through a dedicated website, and will be allocated to either the “parenteral nutrition” or the “oral feeding” group. After randomization, the patient will be given the appropriate patient-information leaflet for the allocated group, after oral information has been provided to the patient.

*Day 1:* The informed consent form, duly signed by the patient and the investigator, will be retrieved by a clinical research assistant. A first consultation will take place at this time to perform standard clinical evaluation and, in particular, to identify and manage any factors that might potentially promote anorexia and digestive disorders. Performance status will be evaluated by using the Karnofsky score, demographic and socioeconomic data will be recorded, and a complete nutritional evaluation, including CRP, albumin, and prealbumin will be performed in all patients. Patients allocated to the parenteral nutrition group will also undergo biological tests before initiation of nutrition. A consultation with a dietitian will be held for all patients. No systematic dietetic follow-up is planned for the study; the cadence of the follow-up consultations is left to the discretion of the relevant healthcare professionals in accordance with their standard practice.

Last, each patient will complete the QLQ-C15-PAL, and patients who are aware of the palliative status of their disease will also complete the QUAL-E.

*From day 1 to day 60:* Patients will have regular follow-up consultations during the follow-up period; at least once per month, based on the patient’s planned attendance at the hospital (for oncology consultations or scheduled admission). The Karnofsky index, quality-of-life evaluation, and details of energy intake will be recorded at each consultation. Nutritional parameters (weight, CRP, prealbumin, albumin) will also be recorded for all patients. Adverse effects will be reported, and serious adverse events will be declared to the relevant pharmacovigilance authorities in the University Hospital of Besancon, France. For patients in the parenteral nutrition group, quantity and duration of nutrition actually administered will be recorded, and complete biological evaluation will be performed (including blood gases, evaluation of phosphorus, magnesium and calcium levels, hepatic enzymes and triglycerides, and evaluation of glycosuria and ketonuria).

Beyond 2 months of treatment, discontinuation or not of parenteral nutrition will be left to the physician’s discretion.

*From day 61 until death*: Quality of life, energy intake, weight, and performance status by using the Karnofsky index will be recorded once per month. Any serious adverse events will be declared to the relevant pharmacovigilance authorities.

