#### *Inclusion and exclusion criteria (Table* 1*)*

**Table 1 Tab1:** **Inclusion and exclusion criteria for participants**

Inclusion criteria	Exclusion criteria
Adult patients (aged >18 years) with cancer at the palliative stage	Any disorder preventing oral ingestion (cancer of the upper aerodigestive tract, esophagus, or stomach)
Specific curative treatment discontinued or still ongoing but with little expected benefit in terms of overall survival	Nonfunctional digestive tract
Life expectancy greater than 2 months	Symptomatic peritoneal carcinosis
Malnutrition defined as Body Mass Index <18.5 kg/m^2^ if age <70 years, <21 kg/m^2^ if age ≥70 years; or weight loss of 2% in 1 week, or 5% in 1 month, or 10% in 6 months	Hematologic malignancies
Patient no longer experiences a sensation of hunger	Myocardial infarction or stroke in the previous 6 months
Patient has lost appetite	Acute renal insufficiency (creatinine clearance < 30 ml/min) or heart failure (left ventricular ejection fraction <30%)
Patient has reduced food intake	Parenteral nutrition ongoing or dating from <1 month
Functional central venous catheter in place	Presence of gastrostomy or jejunostomy
Functional digestive tract	Persisting sensation of hunger
Patient able to understand and speak French	
	Inability to complete quality-of-life questionnaires (due to psychiatric disorders, attention disorders, or cognitive disorders).
	Patients participating in another ongoing trial
	Adult patients under legal guardianship

Inclusion criteria are as follows: adult patients (aged >18 years) with cancer at the palliative stage (that is, patients in whom the main aim of treatment is to limit pain and discomfort). In these patients, curative treatment either has been discontinued, or may still be ongoing but with little expected benefit in terms of overall survival. Life expectancy must be longer than 2 months. To be eligible, patients must have a functional digestive tract and present malnutrition [15–17], defined as a body mass index (BMI) <18.5 kg/m^2^ in patients aged <70 years or <21 kg/m^2^ in patients aged ≥70 years; or weight loss of 2% in 1 week, 5% in 1 month, or 10% in 6 months. Patients with antalgic radiotherapy or scheduled to undergo palliative surgery may be included. Patients must already have a functional central venous catheter in place.

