### Assignment of interventions

The study will comprise two arms: one intervention group (parenteral nutrition group) and one control group (oral feeding group). The Zelen single-consent design requires that consent be obtained only from the intervention group, for their participation in a study involving initiation of parenteral nutrition. The patient will be informed of the study requirements (inclusion criteria, aims, composition, expected effects and benefits, foreseeable risks, contraindications and so on) to allow them to decide whether to consent to participate. The information delivered to the patient will not mention randomization. Patients allocated to the oral feeding group will be informed about their management, and will consent only to completion of the quality-of-life questionnaire. Patients randomized to the intervention group may refuse to consent to the intervention, in which case, they will be included in the control group.

The distribution of patients between the study arms will be performed by the investigator during the first consultation to verify eligibility criteria, by means of Internet access to a 1-to-1 randomization list, balanced by center, and generated automatically by using SAS software (version 9.3; SAS Institute Inc., Cary, NC, USA) and administered by the Clinical Investigation Centre of the University Hospital of Besancon, France.

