#### Primary objective

A treatment group will be considered as superior to the other if at least one of the three domains of the primary end point (physical function, overall health status/quality of life, or fatigue) of the QLQ-C15-PAL questionnaire is clinically and statistically significantly better, without any clinically and statistically significant deterioration in at least one of the other two domains.

Comparison of the three domains of the QLQ-C15-PAL questionnaire (between the parenteral nutrition and oral feeding groups) will be performed on an intention-to-treat basis for all patients randomized and included, by using ANOVA on scores at 2 months. Analyses will be adjusted for the presence (or not) of palliative chemotherapy. The variation in the score for each domain between inclusion (day 1) and day 60 will be compared with ANOVA, taking into account stratification variables and potential confounding factors, such as center, type of cancer, and patient characteristics.

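### The article gives two different times for randomization, and its primary analysis set can be read as a subset formed after the arm is known

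*Protocol article*

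**What the plan says.** **Timing in the time schedule.** Under Time schedule for participants, in the day -7 to day 0 paragraph, "Patients who meet the inclusion criteria will be identified from medical files or from regular staff meetings or multidisciplinary case reviews". This task falls to an oncologist or palliative care physician. The next step is "Once identified, eligible patients will be randomized through a dedicated website, and will be allocated to either the" parenteral or oral group, followed by the information leaflet for that group. The Day 1 paragraph then states: "A first consultation will take place at this time to perform standard clinical evaluation".

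**Timing in the assignment section.** Assignment of interventions states: "The distribution of patients between the study arms will be performed by the investigator during the first consultation to verify eligibility criteria".

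**Eligibility check.** Table 2 begins with "Pre-randomization (day -7 to day 0): Check inclusion and exclusion criteria" and puts randomization after it. Estimated life expectancy, height and weight first appear in Table 2 under Day 1, in columns already split by arm.

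**Analysis set.** The Statistical analysis section applies intention to treat to all analyses. The Primary objective section says that the three-domain comparison "will be performed on an intention-to-treat basis for all patients randomized and included", and a few lines later equates inclusion with day 1.

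**Consent.** Under Assignment of interventions and Information and consent, patients in both arms agree to the quality-of-life questionnaire only after allocation.

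**The concern.** In a Zelen trial, randomization precedes consent by design, and here the arm is open from that moment. Protection against selection therefore rests on two things: eligibility must be settled before the allocation is seen, and nobody may leave the analysis set afterwards for reasons that could depend on the arm. The article leaves both open.

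Under the time-schedule order, no patient contact is described before allocation. Yet several criteria in Table 1 would normally be confirmed with the patient, for example "Patient no longer experiences a sensation of hunger", loss of appetite, or ability to complete the questionnaire. If such a criterion is looked at again on Day 1, that happens with the arm known. If the primary set then counts only patients who reached inclusion on Day 1, the two arms may no longer be the groups that randomization created.

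**Working it through.** The plan gives no figure on this point. The check is a side-by-side reading, followed by an illustration.

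**1. Order of events**

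| Step | Time schedule and Table 2 | Assignment of interventions |
|---|---|---|
| Candidate found | files, meetings, case reviews; day -7 to 0 | not described |
| Eligibility check | before randomization; no patient contact described | in the first consultation |
| Randomization | day -7 to 0, once identified | in the first consultation |
| First consultation | Day 1, after randomization | same occasion as randomization |

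The sources agree that eligibility comes before allocation. They disagree on whether the first consultation comes before or after it, and so on whether the check is made with the patient present.

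**2. Day 1 items that bear on eligibility.** Life expectancy above 2 months is an inclusion criterion. Height and weight give the body mass index in the malnutrition criterion. All three are first scheduled on Day 1.

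**3. Meaning of inclusion.** The Primary objective section dates inclusion to day 1, and the Primary outcome section offers the first questionnaire at inclusion. Under the time schedule, inclusion is thus a later step than randomization, and patients who are both randomized and included can be fewer than those randomized. The word is also used differently: Assignment of interventions says that patients who refuse parenteral nutrition are included in the control group.

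**4. Illustration of size.** From Sample size and recruitment: 70 per group, SD 11, two-sided alpha 0.0166, target 10 points. Assumed, because the documents give no such figures: shares dropped e1 and e0 in the two arms, and a gap D between dropped and retained patients, equal in both arms.

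- Bias = (e1 − e0) × D
- SE = 11 × √[1/(70(1 − e1)) + 1/(70(1 − e0))]
- Critical value z = 2.395
- Two-sided error = 1 − Φ(z − bias/SE) + Φ(−z − bias/SE)

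Middle case, 15% v 5%, D = 15: bias = 0.10 × 15 = 1.5 points; SE = 11 × √(1/59.5 + 1/66.5) = 1.963; bias/SE = 0.764; error 0.052.

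| e1 | e0 | D | Bias (points) | Error per domain |
|---|---|---|---|---|
| 15% | 5% | 0 | 0 | 0.0166 |
| 10% | 5% | 10 | 0.5 | 0.020 |
| 15% | 5% | 15 | 1.5 | 0.052 |
| 20% | 5% | 20 | 3.0 | 0.186 |

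These errors concern the P value alone. The superiority rule asks for a difference that is also clinically significant. If that means an observed difference of at least 10 points, bias of this size would rarely produce a false claim by itself: in the middle case the threshold lies (10 − 1.5)/1.963 = 4.3 standard errors away. The estimate would still be shifted.

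**The case against.** The strongest reply is that the article does protect eligibility. Table 2 puts the check ahead of randomization, and the time schedule speaks of eligible patients being randomized. The person who identifies the patient is the oncologist or palliative care physician, who may already know the patient's appetite, intake, language and cognitive state. Day 1 is described as clinical evaluation, not as a second screening, and recording life expectancy or weight there does not show that it is first judged there. On the analysis set, the same sentence says intention to treat, the general statement repeats it, and the details may sit in an analysis plan that is not shown.

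Most of this stands. A reader might infer that patients are in fact randomized from files alone, that several criteria can only be checked afterwards, and that the analysis discards those found ineligible. The documents do not support that. One section places randomization in the consultation, the need for patient contact is an inference, and no passage states an exclusion rule.

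Nor do they support the inference that the bias would favour parenteral nutrition. An investigator reluctant to start it need not declare the patient ineligible. The article lets patients refuse, in which case they are followed as controls, and lets the investigator or patient stop parenteral nutrition at any time.

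What the reply does not remove is the conflict over the order of events, or a primary set worded with a second condition that the article itself dates after allocation. Both are statements on the page, not omissions left to another document.

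**Conclusion.** The article contradicts itself on when randomization takes place, and its primary analysis set is worded so that it can be read as a post-allocation subset. With open arms and consent after allocation, this leaves a route for selection that knows the arm. Whether the route would be used, in which direction and how strongly cannot be determined from the documents. The 0.5 to 3 points shown above rest wholly on assumed dropout shares and gaps, and there is no bias if the dropped patients do not differ in outcome.

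Loss of scores because a patient declines the questionnaire is a related but separate matter. It arises from consent after allocation in both arms, whatever the order of screening, and better wording of the analysis set will not recover those scores.

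The point should be corrected: the remedy is cheap and leaves randomization before consent intact.

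**What to change.** 1. Reconcile the day -7 to 0 and Day 1 paragraphs of the time schedule with Assignment of interventions, so that one order applies. Every criterion, including estimated life expectancy, is confirmed and entered on the randomization website before it releases the allocation. In Table 2, show estimated life expectancy, and the height and weight used for eligibility, before randomization.
2. In the Primary objective section, drop the second condition and define the set as every randomized patient, analysed in the group assigned.
3. Report by arm the number later found ineligible and the number declining the questionnaire. Keep both in overall survival as far as consent and law allow, and handle absent questionnaire scores as missing outcome data.

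The cost is protocol wording and an eligibility checklist on the existing website. Assignment of interventions already provides a consultation to verify eligibility, so no extra visit follows. The small downside is that eligibility must be confirmed directly with the patient, not only from the file, before randomization.

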### Assignment of interventions

The study will comprise two arms: one intervention group (parenteral nutrition group) and one control group (oral feeding group). The Zelen single-consent design requires that consent be obtained only from the intervention group, for their participation in a study involving initiation of parenteral nutrition. The patient will be informed of the study requirements (inclusion criteria, aims, composition, expected effects and benefits, foreseeable risks, contraindications and so on) to allow them to decide whether to consent to participate. The information delivered to the patient will not mention randomization. Patients allocated to the oral feeding group will be informed about their management, and will consent only to completion of the quality-of-life questionnaire. Patients randomized to the intervention group may refuse to consent to the intervention, in which case, they will be included in the control group.

The distribution of patients between the study arms will be performed by the investigator during the first consultation to verify eligibility criteria, by means of Internet access to a 1-to-1 randomization list, balanced by center, and generated automatically by using SAS software (version 9.3; SAS Institute Inc., Cary, NC, USA) and administered by the Clinical Investigation Centre of the University Hospital of Besancon, France.

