### Trial design

We initiated a multicenter, prospective, 1:1 randomized, controlled, parallel-group trial. The experimental arm consists of initiation of supplemental parenteral nutrition. The control arm consists of pursuing oral feeding alone.

To minimize the difficulty of obtaining informed consent and to stimulate accrual, we used the Zelen single-consent design [14] to randomize patients before informed consent has been obtained. After randomization has been performed, only patients allocated to the intervention group are approached and asked to consent to the study intervention (parenteral nutrition in this case). According to Zelen, patients allocated to the control group and receiving the standard of care (oral feeding in this case) do not need to be informed because these patients are simply going to receive the usual therapy, and therefore, do not constitute a “study population”. Patients allocated to the intervention group who refuse consent are reassigned to the control group.

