#### Sample size and recruitment

In a bilateral situation, a *P* value of <0.0166 will be considered clinically and statistically significant after Bonferroni adjustment for multiple testing, to ensure an overall bilateral alpha risk of 5%. To detect the minimal clinically significant difference (at least 10 points, with a standard deviation of 11 points), with a bilateral alpha risk of 0.0166 and a power of 80%, 54 patients per group are required. Interim analysis to evaluate the primary hypothesis is planned when half the patients have been included and have at least 2 months of follow-up. This interim analysis will be performed according to the rules established by O’Brien and Fleming (Alpha Spending Function with bounds calculated by O’Brien’s method) [24].

The calculation of the sample size takes into account the specificity of the randomization by the Zelen design, and the primary end point of quality of life measured with a multidomain questionnaire: Two groups of equal size, constituted by random assignment; one group will receive standard therapy, and the other group will receive the experimental therapy, or standard therapy if the patients refuses to consent to experimental therapy. The heterogeneity of the intervention group will increase the variance of the difference (Δ_z_) between groups for the primary end point, as compared with classic randomization (Δ_c_), albeit without introducing a measurement bias. The increase in variance will increase with the percentage (Φ) of subjects who receive standard treatment in the intervention group, with [25].

In these conditions, the number of subjects must be multiplied by (1/(1 - Φ)^2^). For the ALIM-K study, we estimate that the percentage (Φ) of subjects who receive standard treatment in the intervention group will be low (estimated at around 10% by experts). Quality of life, as measured by the questionnaire, will yield a score for each domain. To take into account the multiplicity of comparisons, the Bonferroni correction will be applied to the alpha risk.A variation in quality-of-life score of at least 10 points (on a scale of 0 to 100) will be considered as clinically significant.

At an alpha risk of 0.0166, power of 80%, and a percentage Φ of 10%, the number of subjects required to detect a difference of at least 10 points (±11) in quality-of-life score is at least 70 per group (54 × 1.25), or 140 patients in total.

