### Statistical analysis

All analyses will be performed on an intention-to-treat basis. A formal statistical analysis plan will be prepared before the database lock. Any deviation from the statistical analysis plan will be detailed and discussed in the study report.

Clinical and sociodemographic variables collected at baseline will be described as mean ± standard deviation (SD) for normally distributed continuous variables, the median (interquartile) range for nonnormally distributed variables and number (percentage) for qualitative variables. The number of health-related quality-of-life questionnaires completed at each measurement point will be reported.

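### The reassignment of patients who refuse parenteral nutrition to the control group conflicts with intention-to-treat and with the sample-size model

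*Protocol article*

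**What the plan says.** Two sections describe refusal as a change of group. Trial design states: "Patients allocated to the intervention group who refuse consent are reassigned to the control group". Assignment of interventions repeats it: "Patients randomized to the intervention group may refuse to consent to the intervention, in which case, they will be included in the control group".

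Three sections imply the opposite. Statistical analysis states: "All analyses will be performed on an intention-to-treat basis". Primary objective describes the comparison of the three QLQ-C15-PAL domains as "on an intention-to-treat basis for all patients randomized and included". Sample size and recruitment starts from two equal groups formed by random assignment, in which "the other group will receive the experimental therapy, or standard therapy if the patients refuses to consent to experimental therapy". There, Φ is the share of the intervention group that receives standard treatment. It is put at about 10% by expert opinion, and the sample is multiplied by 1/(1−Φ)² because of it.

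The section on discontinuing or modifying allocated interventions keeps patients in their randomized group, but only after a later change of feeding or a serious adverse event. It does not cover refusal at consent.

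**The concern.** The two sets of statements give different answers to a basic question: in which arm does a patient count who was randomized to parenteral nutrition and declined it? The sample-size section works only if that patient stays in the parenteral nutrition arm, because the inflation pays for the dilution such patients cause. If they move, refusal causes no dilution and the inflation has no basis.

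Moving them would also undo the randomization for this subgroup. Acceptors would be compared with all controls plus the refusers. Refusal is the patient's own choice, made after allocation, and the Discussion itself expects to find factors that predict it. If any of those factors also bear on quality of life or survival, the difference between arms is no longer attributable to nutrition alone. A larger sample does not remove that bias.

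A related weakness is the phrase that restricts the primary analysis to patients randomized and included. The article does not define inclusion. Consent follows allocation in both arms, so the phrase can be read as allowing exclusions after randomization.

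**Working it through.** **Inputs from Sample size and recruitment:** 54 per group before inflation; Φ = 10%; 70 per group after inflation; SD 11; two-sided alpha 0.0166 per domain (critical value 2.395). **Assumption:** d, the difference in mean score between acceptors and refusers when nutrition has no effect. The article gives no value, so a range is shown.

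**1. The plan's inflation.** 1/(1 − 0.10)² = 1/0.81 = 1.235, so 54/0.81 = 66.7, or 67 per group. The article uses 54 × 1.25 = 67.5 and states at least 70. So 70 covers the dilution from 10% refusal, provided refusers stay in their arm: an effect of 10 points in acceptors becomes 10 × 0.9 = 9 points between arms. (The starting figure of 54 does not reproduce from the stated inputs, which give about 26 per group. That is a separate matter, and nothing here depends on it.)

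**2. Group sizes if refusers are moved.** Parenteral nutrition: 70 × 0.9 = 63. Control: 70 × 1.1 = 77.

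**3. Share of refusers in the enlarged control group.** By randomization, about 7 of the 70 original controls would have refused if offered parenteral nutrition. Another 7 are moved in. The share is 14/77 = 0.182, or in general 2Φ/(1+Φ).

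**4. Bias with no treatment effect.** Set the acceptor mean at 0 and the refuser mean at −d. The parenteral nutrition mean is 0 and the control mean is −0.182 × d, so the spurious difference is 0.182 × d. With refusers kept in their arm, both means are −0.10 × d and the difference is 0.

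**5. Type I error on the p-value alone.** With SD 11 in both groups, SE = 11 × √(1/63 + 1/77) = 1.87. At d = 10 the shift is 1.82/1.87 = 0.97 SE, and P(Z > 2.395 − 0.97) + P(Z < −2.395 − 0.97) = 0.078. If the control variance is raised for the mixture, to 11² + 0.182 × 0.818 × d², the result is 0.074.

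| Φ | assumed d | bias (points) | per-domain type I error, p-value only (mixture variance) |
|---|---|---|---|
| 10% | 0 | 0 | 0.0166 |
| 10% | 5 | 0.9 | 0.030 |
| 10% | 10 | 1.8 | 0.074 |
| 10% | 15 | 2.7 | 0.154 |
| 20% | 10 | 3.3 | 0.242 |
| 30% | 10 | 4.6 | 0.457 |

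With SD 15.9, close to the value of about 16 that 54 per group would need, the Φ = 10%, d = 10 figure is 0.043.

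**6. Type I error if the observed difference must also reach 10 points.** At Φ = 10% and d = 10, with the mixture variance, SE = 1.92 and P(Z > (10 − 1.82)/1.92) is about 0.00001. At Φ = 10%, d = 20 it is about 0.001, and at Φ = 30%, d = 10 about 0.004. All are below 0.0166. Only larger combinations exceed it: Φ = 20%, d = 20 gives about 0.06.

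**The case against.** The strongest reply is that the analysis text already points to analysis by allocated arm. Intention-to-treat is stated twice, and the sample-size section counts refusers in the intervention group. The two reassignment sentences sit under design and assignment headings and do not mention analysis, so they may mean only that refusers receive control care. A reader might infer that the plan has settled on an as-treated comparison. The documents do not support that: it is what follows if one set of sentences is taken literally, against the stated analysis principle. What remains is that both sentences speak of group membership, that the sample-size section speaks of receiving standard therapy when treatment is meant, and that no sentence reconciles them. This is also not a detail left to the analysis plan, since the article states two incompatible rules and an analysis plan could cite either.

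A reader might also infer that the trial's false-positive rate is 7–8% or more. That does not follow. The figure needs an assumed d, and it ignores the Primary objective rule that a domain be clinically as well as statistically better, with 10 points set under Outcomes. With that rule applied, a false claim at the planned refusal rate is very unlikely. The protection is not firm, however, because the sample-size section also treats a P value below 0.0166 as in itself clinically and statistically significant.

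Third, the plan also compares change from day 1 to day 60. A stable gap in level between acceptors and refusers would cancel there. It would not cancel in the 2-month scores, and a difference in prognosis would not cancel in overall survival.

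Finally, deleting the restriction to included patients would not by itself supply data. Quality-of-life assessment needs consent in both arms after allocation, and patients who decline it have no primary outcome.

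**Conclusion.** The point holds as a conflict in the current text. Two sections move refusers to the control group, while the intention-to-treat statements and the sample-size model require them to stay where they were randomized. Analysis by allocated arm is the better-supported reading, but the article does not secure it.

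If the reassignment wording governed the analysis, the bias at 10% refusal would be 0.18 × d: 0.9 to 2.7 points for assumed d of 5 to 15, which is modest against the 10-point threshold, and zero if refusers and acceptors have the same prognosis. It grows with refusal, to 4.6 points at 30% for d = 10. On the p-value alone, the per-domain type I error at 10% refusal and d = 10 would be about 7–8% instead of 1.66%. With the 10-point criterion also applied, false claims at the planned refusal rate are rare. Whenever d is not zero, the effect estimate remains biased under either success rule, and so does overall survival if survival prognosis differs between acceptors and refusers. The sign of d is unknown, so the direction of bias is too.

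**What to change.** - In Trial design and Assignment of interventions, replace the reassignment sentences with, for example: *Patients who refuse parenteral nutrition receive the care of the control group but remain in, are followed in and are analysed in the arm to which they were randomized.*
- In Primary objective, define the primary analysis set as all randomized patients by allocated arm. Report the number in each arm who decline questionnaire consent, and treat them as having missing outcomes instead of removing them from the set. State that overall survival uses the same arm definition.
- Optionally, if the effect in acceptors is of interest, add a complier-effect estimate as a secondary analysis: the intention-to-treat difference divided by one minus the proportion refusing. It assumes that refusal affects outcome only through the treatment received, and the divisor needs adjusting if controls start parenteral nutrition.

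The cost is wording in the protocol and analysis plan. No extra patients are needed on this account, since the dilution from 10% refusal is already covered by the planned 70 per group.
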